### **Other Analyses**

A sex- and gender-based analysis will be completed when analyzing data for Phases 1 and 2. An economic evaluation of the Thought Spot intervention compared to usual care will also be explored to determine the potential cost-effectiveness and financial implications of sustainable and widespread use of Thought Spot throughout Canadian postsecondary campuses. The primary outcome to be assessed will be the change in helping-seeking intentions among the target population.

A cost-effectiveness analysis will be conducted to compare the cost and outcome of the intervention arm against usual care. The main output will be an incremental net benefit of the intervention compared to usual care [39] and an incremental cost for one point improvement in the GHSQ in a form of an incremental cost-effectiveness ratio. We will characterize the uncertainty of the findings using 95% confidence interval and a cost-effectiveness acceptability curve [40].

Usefulness, satisfaction, ease of use, acceptance, feasibility and performance will be analyzed through the end-of-study usability survey. Results will be analyzed using means and standard deviations of all respondents for each category of the questionnaire. The proportions of participants reporting high,

medium, or low levels of satisfaction will also be calculated. The open-ended survey questions will be analyzed thematically. The findings may be correlated with the other study surveys and digital data to explore the possible influence of usage, acceptance and perceived functioning of the app upon help-seeking behaviours and help-seeking attitudes of participants.

Qualitative analysis will be conducted for the end-of-study qualitative interviews. All interviews will be audio recorded, transcribed verbatim and uploaded to NVivo. The research team will each read through data for emerging themes to develop a coding scheme. When complete, RA will code transcripts to identify major themes. We will use the thematic analysis process described by Braun & Clarke (41) to review the transcribed interviews, generate codes, develop themes and finally present the findings in a final report. The process is outlined below:

1. Audio-recorded interviews will be transcribed verbatim and uploaded to NVIVO by the RA.
2. The research team will gather to read through several transcripts to identify codes across the whole body of transcripts. These codes identify features of the data that are interesting to the analyst, and refer to a segment of the transcript that refers to the concepts such as enablers and barriers to use, app feasibility, acceptance, performance, help-seeking intentions, help-seeking behaviours and attitudes, health literacy, self-efficacy and empowerment. By the end of this phase the research team will have developed a coding tree in NVIVO .
3. The research team arranges different codes into potential themes, by collating all the relevant coded data extracts within the identified themes.
4. In this step we will conduct two levels of reviews and refinement our themes. Level one involves verifying of all codes within one theme to form a coherent pattern. Level two involves a similar process, but in relation to the entire data set.
5. Detailed analysis of themes to ensure there is no thematic overlap between the themes developed in step four.
6. Producing the final report.

## Protocol Change Log

The following amendments were made to the trial protocol after initial approval by the REB.

| Protocol Version                             | Date           | Description of Amendments                                                                                                                                                                                                                                                                                                                                                                                                                                                                                                                                                                                                                                                                                                                                                                                                                                                                                                                                                                                                                                                                                                                                                                                                                                                                                                                                                                                                                                                                                                                                                                                                                                                |
|----------------------------------------------|----------------|--------------------------------------------------------------------------------------------------------------------------------------------------------------------------------------------------------------------------------------------------------------------------------------------------------------------------------------------------------------------------------------------------------------------------------------------------------------------------------------------------------------------------------------------------------------------------------------------------------------------------------------------------------------------------------------------------------------------------------------------------------------------------------------------------------------------------------------------------------------------------------------------------------------------------------------------------------------------------------------------------------------------------------------------------------------------------------------------------------------------------------------------------------------------------------------------------------------------------------------------------------------------------------------------------------------------------------------------------------------------------------------------------------------------------------------------------------------------------------------------------------------------------------------------------------------------------------------------------------------------------------------------------------------------------|
| 1.0                                          | 25 May 2017    | Initial Approval by Research Ethics Board                                                                                                                                                                                                                                                                                                                                                                                                                                                                                                                                                                                                                                                                                                                                                                                                                                                                                                                                                                                                                                                                                                                                                                                                                                                                                                                                                                                                                                                                                                                                                                                                                                |
| 2.0                                          | 3 October 2017 | 
 
Randomization/Blinding: Utilization of the randomization module within REDCap instead of a computer-generated random allocation website (Research Randomizer website). These approaches are considered equivalent
 
Data Collection: Added 6-week and 18-week reminders sent using REDCap online survey platform to support ongoing engagement with study
 
Safety Monitoring: Removal of monthly review of accrued data as there is no interim analysis in the study
 
                                                                                                                                                                                                                                                                                                                                                                                                                                                                                                                                                                                                                                                                                                                                                                                                                                                                                                                                                                                                                                                                                                                                    |
| Participant recruitment for RCT began |                |                                                                                                                                                                                                                                                                                                                                                                                                                                                                                                                                                                                                                                                                                                                                                                                                                                                                                                                                                                                                                                                                                                                                                                                                                                                                                                                                                                                                                                                                                                                                                                                                                                                                          |
| 3.0                                          | 8 August 2018  | 
 
Study title: Updated title on protocol to official title of the study: "Bridging the gap – Tools for finding health, mental health and wellness resources for university and college students"
 
Study Summary: An additional usability survey and end-of-study qualitative interviews were added for participants randomized to the intervention arm. As both study arms will still be receiving and completing the same 6-month follow up survey prior to the additional component, it should not influence or confound study results.
 
Sample Size: Additional verbiage was added to describe and justify the sample size for the usability survey and end-of-study qualitative
 
Recruitment: Additional verbiage was added to describe the recruitment approaches for the usability survey and end-of-study qualitative interviews. These approaches do not impact the recruitment of the overall RCT.
 
Scales/Measures: The Usefulness, Satisfaction, and Ease of Use (USE) Questionnaire will be used for assessing usability of Thought Spot and was added to the protocol. The survey will be administered at the end of the study (6-month follow up).
 
Data collection (End-of-Study Qualitative Interviews): an additional section was added to describe the sampling and data collection approach for the end-of-study qualitative interviews.
 
Safety Consideration and Risks/Adequacy of protection against risks – Additional information regarding risks and adequacy of protection against risks was added for the end-of-study qualitative interviews
 
 |

|     |                  |                                                                                                                                                                                                                                                                                                                                                                                                                                                                                             |
|-----|------------------|---------------------------------------------------------------------------------------------------------------------------------------------------------------------------------------------------------------------------------------------------------------------------------------------------------------------------------------------------------------------------------------------------------------------------------------------------------------------------------------------|
|     |                  | 
 
Confidentiality (Qualitative interviews, data storage) – Additional information was added to describe the storage and protection of confidentiality for the end-of-study qualitative interviews
 
Analysis (other analysis) - The analysis approach for the usability surveys (descriptives) and end-of-study qualitative interviews (thematic analysis) was added.
 
                                                                |
| 4.0 | 4 September 2018 | 
 
Sample Size – Additional verbiage was added to ensure adequate power is maintained for the analysis of the study. The power for our study was calculated using a 60% response rate. To prevent dropping below the 60% response rate required, we will examine the response rate of our 6-month (T2) follow-up survey in October 2018. If the response rate drops below 65%, we will recruit an additional 50 participants into the study.
 
 |

## Statistical Analysis Plan Change Log

The following clarifications and analysis were made to the Statistical Analysis Plan listed in the preceding protocol and the published protocol paper published (1).

- In addition to the listed primary outcome of formal help-seeking scores as measured by the GHSQ (Page 17), we conducted an analysis of the help-seeking scores from informal sources as measured by the GHSQ as part of secondary analyses.
- Help-seeking behavior, as measured by the AHSQ, is separated into formal and informal sources, and was analyzed separately as part of secondary analyses.
- In the Power Calculation, a minor correction is made. “Cronbach alpha level of 0.05” actually means “Significance Level 0.05”
- Clarification is made to ‘Linear Contrast’ in the Power Calculation section. The linear contrast mentioned here refers to the difference in change from baseline to the end of the trial. This is the same as our primary test for the efficacy of our outcome
- In our analysis, there was consensus with the research team and literature that gender can affect help-seeking abilities (2, 3). As such, we controlled for gender across all analysis. This may explain part of the variance in the outcome, increasing power. Controlling for gender was not relevant for the conclusions we present as they were the same when not controlling for gender (results not shown).
- To ensure our results are robust, we conducted model diagnostics analysis which includes autoregressive covariance structure instead and in addition to random effect, looking at residuals, Cook’s Distance, Leverage and DFBetas statistics to access outliers, atypical and influential points. Several large values were identified and removal of these values had no impact on our conclusion and no meaningful change in model coefficients. We also inspected the data visually for outliers and normality through the liberal use of graphs.
- An extra sensitivity analysis was conducted where baseline variables significantly associated with dropouts at significance level of 0.20 were added to the primary model. Under the direction of our senior statistician, this is considered a better alternative than the one listed in the protocol which uses completers only. That is because mixed effect models adjusted by maximum likelihood can correct biases caused by missing values as long as the missing values are not associated with information not in the model (Missing At Random – MAR – assumption). By adding baseline variables associated with missing values we increase our chances that we are not violating the MAR assumption. The high level 0.20 was chosen so that we minimize the chances of missing important variables, having in mind that in this case we are more concerned with missing important variables than with including unimportant variables. This was only done for the primary outcome, and reported in our paper. The sensitivity analysis described in the protocol, which keeps only completers, was also conducted and the conclusion was the same.
- Multiple comparisons was not conducted so we did not need to use Bonferroni adjustments. Our secondary analyses are conducted with exploratory nature.

- Since there was no evidence for our primary outcome, we did not conduct the sex- and gender-based analysis.
- We conducted two additional exploratory analyses that are important for the completeness of our analysis and may be of interest to researchers.
  - Per-protocol analysis - In the per-protocol data analysis, we repeated our primary analysis holding in the intervention arm only subjects who logged onto Thought Spot more than once were considered, as a definition of compliance. As an extension of this analysis, also looked at the moderation effect of compliance.
  - App Usage Analysis – We conducted a descriptive analysis of usage on Thought Spot.
- Blinding: The senior biostatistician analyzing the data was blinded to the treatment group, except for the per-protocol analysis which was conducted last.

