## Study Summary

The onset of mental illness across the lifespan is highest among children and youth, with 70% of cases emerging before age 24 [1]. Despite the benefits of early identification and treatment, at-risk members of this age group have great difficulty accessing and receiving the mental health services they need [2-6]. With more than 90% of youth using the Internet [7-9], web-based electronic health (eHealth) and mobile-based health (mHealth) interventions are promising tools for reaching this age group [10-15], potentially bridging the gap for hard-to-reach populations such as young males or other transition-aged youth who have been reluctant to seek services [16-18]. Within this study we define transition-aged youth as those aged 16-29.

Using a partially blinded, two-arm randomized control study design, this project will test the hypothesis that transition-aged youth who use Thought Spot, a youth-driven open-source online and mHealth intervention, will have greater improvement in self-efficacy and intentions towards help-seeking for mental health concerns compared to a control group. The study will also examine whether participants in the intervention arm show greater improvements in health literacy, including awareness of available services and supports, increased self-efficacy in managing their mental health concerns, and a reduction in mental health stigma, compared to the control arm. Participants in the intervention arm will have access to the Thought Spot platform (online and mobile versions), while the control arm will receive usual care (access to campus health services, Web- and print-based information materials).

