**Sample size**

To determine the sample size required to test the primary hypothesis that the Thought Spot intervention will cause a greater change in help seeking intentions compared to usual care, as measured by the difference in formal help seeking intentions from 6 months to baseline, a series of Monte Carlo simulations were carried out (with 10000 replications under each test scenario) using SAS System for Windows v.9.4 (SAS Institute Inc. Cary, NC). These simulations assume that the primary hypothesis will be tested using Mixed Effect Models to account for the longitudinal design and contrasts using time and arm to compare the changes from baseline in both arms. We assume that the test will be two tailed and with critical alpha level of 0.05. In order to simulate the data, means and standard deviation, as well as within subject association are assumed to follow published data that used similar study design. A small effect size, equivalent to a Cohen's d of 0.25, was considered (i.e., an average change in the Help-Seeking Scale of 0.41 - which is a change of 15%), within subject correlation of 0.6, attrition rate of 40% and power of 80%. Based on these simulations and specifications, a sample of 236 subjects per arm before attrition should be used.

To prevent dropping below the 60% response rate required, we will examine our response rates for the final T2 surveys (6 month survey) when the first block of approximately 50-100 participants completes the T2 survey at the 6-month mark of the study. We are proposing to recruit an additional 50 participants if we drop below a 65% response rate at that point. The rationale for this decision is to maintain the power for the analysis in this study.

The participants in the intervention arm will be invited to a usability survey at the 6-month mark which measures usefulness, satisfaction and ease of use of the Thought Spot application. The sample for this survey is limited to the intervention arm because only these participants had access to the Thought Spot application.

A purposeful sample of 15-20 participants who completed the usability survey will be invited to participate in a 30 minute in-person or telephone qualitative interview to better understand enablers and barriers to using Thought Spot and its impact on help-seeking intentions, health literacy, self-efficacy and empowerment. The purposeful sampling criteria follows:

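### The planned sex- and gender-based analysis was left undone because the primary result was null, which is a disclosed but result-dependent departure made for a reason that does not hold

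*Protocol*

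**What the plan says.** The Other Analyses section commits to the work in one sentence: "A sex- and gender-based analysis will be completed when analyzing data for Phases 1 and 2". It names no model, outcome or contrast, and it does not make the analysis depend on the primary result. No other section adds such a condition.

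The Statistical Analysis Plan Change Log then records: "Since there was no evidence for our primary outcome, we did not conduct the sex- and gender-based analysis".

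The same log describes how gender was used. It says that "there was consensus with the research team and literature that gender can affect help-seeking abilities", and continues: "As such, we controlled for gender across all analysis". It adds that the conclusions were the same without that adjustment. It describes no estimate by gender and no interaction of gender with arm.

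The log also reports a per-protocol analysis that keeps, in the intervention arm, only participants who logged on more than once. As an extension, the authors "also looked at the moderation effect of compliance".

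The Study Summary motivates digital tools partly as "potentially bridging the gap for hard-to-reach populations such as young males", and goes on to mention other reluctant transition-aged youth.

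**The concern.** The analysis was planned without regard to the primary result and dropped because of it. The log gives no other reason, such as too few participants in one category.

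The reason does not bear the weight put on it. The primary contrast averages the intervention effect over genders, so a benefit in one gender and none in the other appears as a smaller average that can easily be non-significant. The question of whether the effect differs by gender is still open after a null primary result.

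At stake is an exploratory question, not the primary conclusion. The trial's background singles out young men, and its team judged gender relevant to the outcome. Yet readers receive no gender-specific estimate to interpret or to pool with other trials.

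**Working it through.** **The text, side by side**

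1. Plan: an unconditional commitment (Other Analyses). Log: not done, because the primary outcome was null. Other Analyses is current text, so the log entry records a deviation from a plan still in force, not a superseded passage.
2. Gender as a covariate shifts the expected score of both arms alike. The arm-by-time contrast remains one number averaged over genders. Agreement between the adjusted and unadjusted models compares two versions of that average and says nothing about effect modification.
3. The null did not end moderation work in general. Moderation by compliance was examined although the plan does not mention it. Compliance is a post-randomisation behaviour applied to one arm. Gender is a baseline variable, so comparing arms within gender keeps the randomised comparison.

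**How often would an effect in one gender give an overall null?**

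The plan gives no figure on this point to reproduce, so the following is illustrative.

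*Inputs from Sample size and Power Analysis:* 236 per arm; 40% attrition by 6 months, leaving 236 × 0.6 = 141.6 per arm (the protocol rounds to 142); within-subject correlation 0.6; d = 0.25; for the test, "We assume that the test will be two tailed and with critical alpha level of 0.05".

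*Assumptions not in the documents:* dropout at 3 months anywhere from 0% to 40%; equal gender halves (then 30% and 20%); equal variance and the same correlation between all visits; d in units of the SD of a single-visit score; no effect in the other gender.

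*Step 1: standard error (SE) of the baseline-to-6-month contrast between arms, by maximum likelihood.*

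- All dropouts gone by month 3: variance per arm = (1 − 0.6²)/141.6 + (1 − 0.6)²/236 = 0.004520 + 0.000678 = 0.005198. SE = √(2 × 0.005198) = 0.1020.
- No dropout before month 3: month 6 is regressed on two earlier visits, each with coefficient 0.6/1.6 = 0.375. Residual variance = 1 − 2 × 0.36/1.6 = 0.55. The remaining part, 0.375 × month 3 − 0.625 × baseline, has variance 0.375² + 0.625² − 2 × 0.375 × 0.625 × 0.6 = 0.25. Variance per arm = 0.55/141.6 + 0.25/236 = 0.004944. SE = √(2 × 0.004944) = 0.0994.
- 20% dropout at month 3 lies between these: SE = 0.1004.
- Taking the stated 80% power as given: SE = 0.25/(1.96 + 0.84) = 0.089.

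The first three SEs imply about 69–71% power at d = 0.25 in everyone. The protocol's 80% comes from simulations whose means and SDs are not shown, so both versions are carried forward.

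*Step 2: effect of 0.25 SD in one half only.* Power = Φ(z − 1.96).

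| Quantity | Formula | SE 0.0994–0.1020 | SE 0.089 |
|---|---|---|---|
| Overall test | z = 0.125/SE | z 1.23–1.26, power 23–24% | z 1.40, power 29% |
| Interaction test | z = 0.25/(2 × SE) | same z, 23–24% | same z, 29% |
| Contrast within the affected gender | z = 0.25/(√2 × SE) | z 1.73–1.78, power 41–43% | z 1.98, power 51% |
| Interaction detectable at 80% power | 2.80 × 2 × SE | 0.56–0.57 SD | 0.50 SD |

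*Step 3: the affected gender is a minority (SE 0.1004).* With share f, the overall z is f × 0.25/SE and the interaction z is 0.25 × √(f(1 − f))/SE.

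- f = 30%: overall z 0.75, power 11%; interaction z 1.14, power 21%.
- f = 20%: overall z 0.50, power 7%; interaction z 1.00, power 17%.

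*Step 4: precision on offer with equal halves (SE 0.1004).* The 95% half-width is 1.96 × √2 × 0.1004 = 0.28 SD for a gender-specific contrast and 1.96 × 2 × 0.1004 = 0.39 SD for the interaction.

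**The case against.** The strongest reply is that little was lost. With equal halves, the interaction test has exactly the same z as the overall test, so it too would miss the assumed effect about three times in four. The detectable interaction, 0.50–0.57 SD, is at least twice the design effect. This stands, and it rules out presenting the omitted analysis as one that would have settled the question. It does not justify the omission. Low power was equally foreseeable when the analysis was planned, and it is not the reason the log gives.

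Second, the plan is thin. It specifies no interaction, it refers to phases that this document does not define, and no objective or hypothesis concerns gender. This also stands: the three-way interaction proposed below is one reasonable reading of the commitment. The log, however, itself treats the analysis as a planned part of this trial.

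A reader might also infer more than the documents support:

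- *That results were hidden or selectively reported.* The omission and its reason are stated openly, and nothing suggests that a gender result was obtained and withheld.
- *That two unplanned analyses replaced the planned one.* The log does say "We conducted two additional exploratory analyses that are important for the completeness of our analysis", but the second, app usage, was already planned under Digital data collection. Only the per-protocol analysis and its moderation extension are new. The log says the per-protocol analysis came last; it does not say that the null prompted it.
- *That a benefit in young men was missed.* Nothing in the documents shows one.

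**Conclusion.** The point holds as a disclosed, result-dependent departure from an unconditional plan, justified by a reason that does not follow. It does not affect the primary conclusion.

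If an effect of d = 0.25 were confined to one of two equal gender groups, the overall test would be null in roughly 71–77% of trials, so the null says little about such an effect. If the affected gender were a minority, overall power would be lower still. These figures rest on the assumed gender split, which matters a good deal, and on the assumed 3-month dropout, which hardly matters. The missing product is a set of gender-specific estimates with honest intervals. A decisive interaction test was never within reach at this sample size.

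**What to change.** Carry out the planned analysis whatever the primary result. Add arm × time × gender, with its lower-order terms, to the primary GHSQ formal-sources model. Report the baseline-to-6-month contrast between arms within each gender, and the interaction, each with a 95% interval and labelled exploratory. State the number of participants in each gender category by arm, and how sparse categories are handled.

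In the Statistical Analysis Plan Change Log, replace the stated reason with a note that the analysis was done, or, if it is still not done, with a reason that does not rest on the primary result. The Other Analyses section contains no condition that needs deleting; it would only gain from naming the model and contrast.

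The cost is one further model on data already held, with gender already in the analysis file. The downside is wide intervals, about ±0.28 SD within gender and ±0.39 SD for the interaction under equal halves. The text should therefore say that a non-significant interaction is not evidence of equal effects.
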